## Blinding

To minimize observer bias, the patients and investigators will be blinded to the treatment assignment to prevent any bias related to the knowledge of the treatment assignment when assessing the outcome. The clinic study team will be blinded to the treatment assignment. The patients will be identified by a study number unrelated to the treatment assignment, and all forms will be standardized regardless of the treatment assignment. If any serious adverse events occur, the Data Safety Monitoring Board will review the data after unblinding.

## Data Safety Monitoring

An independent Data Safety Monitoring Board (DSMB) will be formed to review the safety in this study. The DSMB will be comprised of three members: a clinician, a clinical pharmacologist and a biostatistician, all independent from the trial. One interim analysis of safety will be performed by the DSMB after safety data are available on twelve (12) patients (6 patients on each randomized arm of treatment). The data will be unblinded for the DSMB review. Any dengue death, admission to the intensive care unit or severe dengue (DHF/DSS) will trigger a data safety review by the DSMB. The decision to terminate the trial prematurely will depend on not just the interim results but other relevant information such as the patients' prognosis and the nature of treatment, as well. Emergency code-break envelopes will be prepared by the randomization statistician and be available for DSMB members. The envelopes will be kept unopened unless unblinding is needed.

The following data will be analysed in the safety assessments: clinical exam (body weight, vital signs); fluid administration; urine output and urinalysis; adverse events including stool frequency and consistency. Adverse events and serious adverse events that will be monitored include but are not limited to the following:

(1) Gastrointestinal side effects such as diarrhea and bloatedness/flatulence.

(2) Severe dengue (DHF/DSS).

(3) Admission to intensive care unit.

(4) Death.

All SAEs which fulfill the above and what is stated in the CIRB LSAE reporting form will be reported to Health Science Authority and Singhealth IRB in accordance with established timelines.

## Data Management

Direct data capture of demographic and clinical data will be conducted using computer notebooks. The data will be kept confidential in password protected computers accessible only by selected research staff. Identifiers will be kept in a separate file in another office and every effort will be made to protect the privacy of the participants. The data to be analyzed will contain only de-identified data. An electronic data capture system will be used. Authorized personnel will be assigned user IDs and passwords to gain access to the database. Data will be entered into database directly by site personnel. Entered data will be systematically checked by built-in edit checks. Data that failed the edit checks will be highlighted to the site personnel for resolution. Data will be managed by SCRI. Electronic data capture will be used. Authorized personnel will be assigned user IDs and passwords to gain access to the database. Data will be entered into database directly by site personnel. Entered data will be systematically checked by SCRI data management staff and validated via database edit checks and database listings. Data queries will be channeled to the responsible parties for resolution.

## Criteria for Discontinuation of Patient Study Drug and for Study Termination

A patient’s study drug will be discontinued for

1) any patient developing severe dengue based on WHO criteria or

2) any patient developing grade 3 severity diarrhoea

The study will be terminated at any time that the Data Safety and Monitoring Board members conclude that:

1) Clear and significant harm is noticed in the treatment;

2) ≥30% serious adverse reactions occur in the treatment arm that are possibly, probably or definitely related to study drug;

3) ≥30% patients develop severe dengue based on WHO criteria;

4) ≥30% patients develop grade 3 severity diarrhoea;

5) The drop out rate is too high (>30%).

Figure 2 Flowchart of patients’ activities

Placebo

(N = 25)

Celgosivir

(N = 25)

Drug administration

Drug administration

Daily assessment

Daily assessment

Return to IMU for assessment

Return to IMU for assessment

Visit to polyclinic or GP/ED of NUH or SGH

Assessment of high probability of dengue infection

Fever ≥38° of ≤ 48 hr duration

≥2 symptoms of dengue fever

Positive NS1 strip assay

Others

Referral to IMU for screening of other inclusion & exclusion criteria

Written inform consent

Baseline assessment

Randomization

Discharge

End of Study

Day 5

Day 1

Day 1 to Day 5

Days 7, 10, 15

Day 15

Prior to Day 1

# Statistical Considerations

## Sample size calculation

To achieve 80% power to detect a difference of one log viremia reduction between the celgosivir treated group and the placebo group, assuming a standard deviation of one log, a sample size of 14 for each group (28 total) is required for a 5% one-sided type I error. With a sample size of 25 in each group (50 total), we are able to detect a difference of 0.7 log viremia reduction at a standard deviation of one log (equivalently a one log reduction at a standard deviation of 1.4 log) at 80% power.

## Statistical analysis

A detailed statistical analysis plan will be prepared prior to unblinding.

General

Continuous variables will be summarized using mean and standard deviation. Categorical variables will be summarized by frequency and percentage. Percentages will be rounded to one decimal place and, therefore, may not always add up to 100. All statistical tests will be set at a 5% level of significance. All confidence intervals will be 95% and two-sided. Statistical analyses will be performed using SAS version 9.3.

Demographic and baseline characteristics

Descriptive statistics will be used to summarize demographics and baseline information and to assess balance between the two groups (mean, standard deviation, minimum, maximum, and median for continuous variables; frequency and percent for categorical variables).

Analysis population

Statistical analysis for efficacy data will be carried out on an intention-to-treat (ITT) basis. An ITT set is defined as all patients who signed the informed consent form for the study enrollment and obtained an enrollment number. The treatment group of patients in the ITT set is the planned treatment group, i.e., according to the randomization list planned prior to the study commencement.

Statistical analysis for safety data will be carried out on an as-treated basis. An as-treated set is defined as all subjects who signed the informed consent form for the study enrollment and obtained an enrollment number. The treatment group of patients in the as-treated set is according to the treatment actually received.

Primary outcome

The primary outcomes include the mean of virological log reduction at Day 2, Day 3 and Day 4 and fever AUC above baseline. The virological log reduction of each patient will be measured at Day 2, Day 3 and Day 4 when they are inpatients. The mean of these three measurements will be computed for each patient, and then be compared between the two groups by a two-sample, one-sided t-test. The body temperature of each patient will be measured at baseline and from Day 1 to Day 5, and a curve of the temperature will be plotted. The area under this curve but above the baseline value will be computed for each patient, and then be compared between the two groups by a two-sample, one-sided t-test.

Secondary outcomes

Viral clearance is indicated by an “undetectable” lab test results in the Dengue PCR at baseline, Day 2, Day 3, Day 4, Day 5 and Day 7. The time from baseline to viral clearance will be analyzed using a Kaplan-Meier analysis.

Serum NS 1 is measured by lab test results of “Dengue Non-structure protein 1”. The mean serum NS 1 between day 2 and Day 5 inclusive will be computed for each patient, and compared between the two groups using linear regression, adjusting for primary vs secondary infection. NS1 clearance is indicated by an undetectable lab test result in the NS1 assay. The time to NS1 clearance will be analyzed using a Kaplan-Meier analysis and compared using log rank test.

Leukocyte is measured by lab test results of “Urinalysis”, while platelet count is measure by the lab test results of “Hematology”. Both outcomes will be measured at baseline, Day 2, Day 3, Day 4 and Day 5. The maximum changes from baseline in leukocyte and platelet counts between Day 2 and Day 5 will be computed for each patient, and compared between the two groups using a two-sample t-test.

Hemoconcentration is defined as the hemaocrit at each day compared to that at Day 15. If the reference value at Day 15 is not available, use the value at Day 10. If both values at Day 10 and Day 15 are not available, the patient will be treated as a missing case. The mean maximal hemoconcentration from Day 2 to Day 5 will be computed for each patient, and compared between the two groups using a two-sample t-test.

Clearance celgosivir and volume of distribution of celgosivir will be obtained from concentration-time date by standard PK analysis. The correlation of these PK parameters with weight, age, and sex will be examined by nonlinear mixed effects modeling.

Exploratory outcomes

The various cytokines including TNF-, IL-6, IL-12, interferon-, and MCP-1, are measured by lab test results of “Cytokines” at Study Days 1, 2, 3, 4, 5, 7, 10, and 15. The maximal change from baseline (Day 1) in these cytokines between Day 2 and 15 will be computed for each patient, and compared between the two groups using two-sample t-test.

To investigate whether patients taking celgosivir will use less analgesic medications during the study, analgesic medications recorded during the in-hospital stay and the out-patient diary will between totaled. The total will be compared between the two groups using Fisher exact test.

To investigate whether patients taking celgosivir will experience a lower intensity of joint and muscle pain during the study, the intensity of joint and muscle pain recorded in the “Pain Score” section during the in-hospital stay and the outpatient diary will be obtained and compared between the two groups using two-sample t-test.

Safety outcome

Safety data will be tabulated according to the standard IMU grading scales for occurrence. The proportion of AEs and SAEs among patients will be reported by cohort.

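### The 95% two-sided intervals do not match the one-sided 5% primary tests, and no rule says how the two primary endpoints together support effectiveness

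*Protocol*

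**What the plan says.** Section 2.1 of the Protocol has one primary objective, the effectiveness of celgosivir in acute dengue fever, with two hypotheses under it: a virological one (greater VLR) and a clinical one (lower fever AUC). Section 3.1 likewise names one primary virological and one primary clinical endpoint. Section 6.2 repeats this: "The primary outcomes include the mean of virological log reduction at Day 2, Day 3 and Day 4 and fever AUC above baseline".

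Each endpoint has its own test. For VLR: "The mean of these three measurements will be computed for each patient, and then be compared between the two groups by a two-sample, one-sided t-test". For fever AUC, the area "will be computed for each patient, and then be compared between the two groups by a two-sample, one-sided t-test". The general paragraph of section 6.2 sets the level for every test and every interval: "All statistical tests will be set at a 5% level of significance. All confidence intervals will be 95% and two-sided".

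Section 6.1 sizes the trial on viremia only: "To achieve 80% power to detect a difference of one log viremia reduction between the celgosivir treated group and the placebo group", with an SD of one log, "a sample size of 14 for each group (28 total) is required for a 5% one-sided type I error". It then gives 0.7 log as the difference detectable with 25 per group.

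None of these sections says whether a conclusion of effectiveness needs both endpoints or only one. None gives a testing order or a division of the 5%. Section 6.2 promises a detailed statistical analysis plan before unblinding; that plan is not at hand.

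**The concern.** There are two separate issues.

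**Interval and test.** A two-sided 95% interval excludes zero on the favourable side exactly when a one-sided 2.5% test rejects. The primary tests are one-sided at 5%. A primary endpoint can therefore be declared significant and be reported with an interval that includes no effect. A reader who relies on the interval and a reader who relies on the test would then draw opposite conclusions from the same data.

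**Two endpoints, one objective.** Each endpoint is given the full one-sided 5%. If a positive result on either were enough to conclude that the drug is effective, the chance of reaching that conclusion for an inactive drug would exceed 5%. If both are needed, it would not. The Protocol leaves both readings open, so a reader cannot say what error rate goes with the effectiveness conclusion.

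**Working it through.** **Inputs.** From section 6.1: one-sided 5%, power 80%, difference 1 log, SD 1 log, 14 per group; then 25 per group with 0.7 log at SD 1, or 1 log at SD 1.4. From section 6.2: two primary outcomes, each with a one-sided two-sample t-test at 5%, and 95% two-sided intervals. The correlation between the two test statistics is not given. It is an assumption here, shown from 0 to 0.9.

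**1. Reproducing the Protocol's own figures.** Power of the two-sample t-test, with n per group and df = 2n − 2, is P(T > t₀.₉₅), where T is noncentral t with noncentrality δ / (σ√(2/n)).
- n = 14, δ/σ = 1: power 82.4%. With n = 13 it is 79.7%. The stated 14 is reproduced.
- A two-sided 5% test would need 17 per group, so the Protocol sized for the one-sided 5% test.
- n = 25, δ/σ = 0.7: noncentrality 0.7 / √(2/25) = 0.7 / 0.2828 = 2.475; power 78.7% (79.7% by the normal approximation).
- n = 25, δ = 1, σ = 1.4: power 80.1%.

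The sample-size statement agrees with the one-sided 5% tests in section 6.2. The interval level is what does not fit.

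**2. Test against interval, 25 per arm, 48 df.**
- The one-sided 5% test rejects at t > 1.677, an observed difference above 1.677 × 0.2828 = 0.474 SD.
- The 95% two-sided interval excludes zero in the favourable direction at t > 2.011, an observed difference above 2.011 × 0.2828 = 0.569 SD.
- For t between the two, the test is significant and the interval includes zero.
- Probability with no true effect: 5% − 2.5% = 2.5% for each endpoint.
- Probability at a true difference of 0.7 SD: power at one-sided 5% minus power at one-sided 2.5% = 78.7% − 67.9% = 10.8%.

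This part needs no assumption about the success rule or the correlation.

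**3. Chance of at least one false-positive primary test, with neither endpoint truly affected.** Under independence: 1 − 0.95² = 9.75%. With correlation ρ: 1 − Φ₂(1.645, 1.645; ρ), where Φ₂ is the bivariate normal distribution function.

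| Assumed ρ | Either endpoint suffices | Both required |
|---|---|---|
| 0 | 9.75% | 0.25% |
| 0.3 | 9.3% | 0.7% |
| 0.5 | 8.8% | 1.2% |
| 0.7 | 8.0% | 2.0% |
| 0.9 | 6.8% | 3.2% |

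Whatever the dependence, the either-endpoint rate cannot exceed 5% + 5% = 10%. When both are required, a false conclusion needs a false rejection on at least one endpoint that has no effect, so the rate never exceeds 5%, even if the other endpoint truly responds.

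**4. What the remedies do.**
- Fixed order, VLR first, each at one-sided 5%: overall error at most 5%, VLR power unchanged at 78.7%. The chance that VLR fails at the planned effect, and fever AUC is not formally tested, is 1 − 0.787 = 21.3%.
- Both required, each at one-sided 5%: overall error at most 5%.
- Equal split, one-sided 2.5% each: error 1 − 0.975² = 4.94% under independence. This also matches the 95% intervals, but power for 0.7 SD falls to 67.9%, and regaining 80% takes 34 per group against 26 at one-sided 5% by the same exact method.

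**The case against.** Four points can be made for the plan.

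- **The success rule may be in the analysis plan.** A rule for combining endpoints is commonly set there, and nothing in the Protocol prevents a fixed order or a both-required rule, since each would still test at 5%. This stands. The missing rule alone is not an error, and the 5% level per test is not wrong in itself. The interval mismatch differs, because the Protocol fixes both the one-sided 5% primary tests and the 95% two-sided level for every interval.
- **This is a 50-patient Phase 1b proof-of-concept trial.** That limits how much error control one should demand. It does not remove the need to say what will count as evidence of effectiveness, because the Protocol sets a type I error and sizes to it.
- **The interval has no decision role.** The primary-outcome text rests the comparison on the t-test, and the 95% level is a general reporting rule. This is right: no error rate changes. What remains is a reporting conflict that the trial would meet with 10.8% probability at the planned effect.
- **A fixed order has a price.** It subordinates the only clinical primary endpoint, although sections 2.1 and 3.1 list the two side by side. That is a real cost and the reason to offer a both-required rule as an alternative.

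A reader might go further and infer that the trial's false-positive rate is about 10%, or twice the rate used for sizing. The documents do not support either. The first holds only if one positive endpoint suffices, which the Protocol neither states nor excludes, and 9.75% also needs independence between two measures of the same illness. The second compares unlike quantities: section 6.1 concerns viremia alone at one-sided 5%, and the VLR test in section 6.2 has exactly that level. Nor is the sample size miscalculated; it reproduces.

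**Conclusion.** The point holds in two parts of different strength.

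The interval mismatch is certain from the Protocol's text. With 25 analysed per arm and an equal-variance t-test, significance and a 95% interval that includes zero will coincide in 2.5% of trials per endpoint with no effect, and in 10.8% at a true 0.7 SD difference. It affects interpretation, not error control.

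The multiplicity part is conditional. The error rate for the effectiveness conclusion is 9.75% under independence, or about 8.0% to 9.3% at assumed correlations of 0.7 to 0.3, if either endpoint suffices. It is at most 5% if both are required, and 5% for each if the two hypotheses are treated as separate claims. The Protocol does not say which applies, so the rule should be stated before unblinding. Both parts are worth correcting; neither undermines the design or the sample size.

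**What to change.** 1. For VLR and fever AUC, report the 90% two-sided interval, or the one-sided 95% bound, as the interval that matches the test. Keep the 95% two-sided interval as additional information and say that it corresponds to one-sided 2.5%.
2. State in the Protocol or the analysis plan, before unblinding, that VLR is tested first at one-sided 5%. Fever AUC is then tested at one-sided 5% for a formal claim only if VLR succeeds, and is otherwise reported descriptively. Stating that both endpoints are required for a conclusion of effectiveness would also cap the error at 5%.

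**Cost.** Wording only: no added patients or assessments. Under the fixed order VLR keeps its power, but fever cannot be formally claimed when VLR fails, which happens about 21% of the time at a true VLR effect of 0.7 SD. Under the both-required rule, neither endpoint alone can carry the conclusion. Splitting the 5% equally would also work and would match the 95% intervals, but it lowers VLR power at 0.7 SD from 78.7% to 67.9%, so it is the less attractive choice with 25 per arm.

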Upon admission, a clinical examination will be conducted, including ECG and chest X-ray. Blood samples will be taken for baseline assessments - viremia, quantitative NS1, IgG specific for previous dengue infection, hematology and coagulation, clinical chemistry, immunological profile, pre-dose pharmacokinetics, and DNA and RNA analysis. Urine will be collected for a pregnancy test (female patients only) and urine protein/ creatinine ratio and urinalysis (all patients). The patient will be asked to complete a visual analog scale for pain (VASP). The patient will then be randomized to placebo or celgosivir group. Capsules will be administered without food from Day 1 to Day 5. Patients will be placed on a special diet of protein, vitamins, and glucose containing minimal complex sugars or starches. Oral fluid intake, urine output, and stool frequency and consistency will be recorded, as well as any adverse events. Daily clinical exams will be conducted. Blood samples will be drawn daily while in hospital for hematology and clinical chemistry, viremia, quantitative NS1 levels, and immunological profiling (RNA expression levels and cytokines). Any subject who has a platelet count drop of ≥50,000/mm3 over a 24 hour period will require full blood count monitoring every 12 hr henceforth until platelet count trend reverses. Urinalysis will be conducted daily, and a sample of urine will be reserved for PK drug levels. Patients also will be asked to complete a VASP daily. Pain medications and any other concomitant medications will be recorded (date/time of ingestion and amount). Over the course of the hospital stay, eight blood samples will be obtained for pharmacokinetic assessments: one pre-dose sample will be taken on Study Day 1, three samples will be obtained on Study Days 2 through 4 between 1 to 3 hr after ingestion of drug (peak levels), and four samples will be obtained on Study Days 2 through 5 immediately prior to ingestion of the next dose (trough levels). The date and time of pharmacokinetic blood draws will be recorded on the CRF. On Study Day 5, after blood draws, administration of the last dose, safety assessments, determination of risk for DHF or DSS, and satisfactory clinical status, the patient will be discharged. Patients at risk for or who have dengue hemorrhagic fever (DHF) or dengue shock syndrome (DSS) will be transferred to a medical ward of the hospital until fit for discharge. Patients who progress to DHF or DSS may require intravenous fluids, platelet and/or blood transfusions and evaluations from other clinical specialists. They will be treated according to standard of care for DHF and DSS--primarily bed rest, fluids, as well as fever and pain medications (supportive therapy).

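### The primary viremia comparison is fixed as an unadjusted t-test on change, although baseline viremia and prior-infection status are in hand before randomization; the test is valid but probably gives up some precision

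*Protocol*

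**What the plan says.** Protocol, Statistical analysis (Primary outcome): "The virological log reduction of each patient will be measured at Day 2, Day 3 and Day 4 when they are inpatients". It continues: "The mean of these three measurements will be computed for each patient, and then be compared between the two groups"; the test is a one-sided two-sample t-test. No covariate is named.

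Other parts of the protocol bear on this choice:

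- **Methods and Assessments.** The blood taken on admission, before randomization, covers viremia and "IgG specific for previous dengue infection".
- **Randomization.** Allocation is 1:1 in permuted blocks, meant to keep the arms balanced over time. No stratification factor is named.
- **Statistical analysis (Demographic and baseline characteristics).** Baseline balance is only described.
- **Statistical analysis (Secondary outcomes).** Mean NS1 over Days 2 to 5 is "compared between the two groups using linear regression, adjusting for primary vs secondary infection". In the same section, "Viral clearance is indicated by an “undetectable” lab test results" in the dengue PCR, from baseline to Day 7.
- **Sample size calculation.** The basis is "To achieve 80% power to detect a difference of one log viremia reduction between the celgosivir treated group and the placebo group" at an SD of one log. The resulting 14 per group "is required for a 5% one-sided type I error". With 25 per group, the stated detectable difference is 0.7 log at an SD of one log.

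A detailed SAP is announced, but the protocol itself already names the primary test.

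**The concern.** The log reduction is baseline minus follow-up. A fall below the detection limit cannot be measured, so a patient who starts low has less room to fall. Baseline therefore enters the outcome, and the change score handles it by implicitly giving it a regression slope of exactly one. If the true slope of follow-up on baseline log viremia differs from one, two things follow:

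- The t-test carries variance that a model could remove.
- Part of any chance difference between the arms at baseline remains in the estimated effect.

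Neither the randomization nor the analysis guards against such a difference. The protocol does adjust for infection status in a secondary endpoint, but not in the primary one.

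What is at stake is power at the smaller effect that the 25 per arm are meant to detect, and a primary result that is easy to dispute if the arms turn out unequal at baseline. An adjustment added after unblinding, once an imbalance has been seen, would be post hoc.

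**Working it through.** **Inputs from the protocol:** 25 per arm, 1:1, one-sided 5%, SD one log (read as the SD of a patient's mean log reduction), differences of 1 and 0.7 log. **Assumed, because the protocol gives no figure:** the correlation r between baseline and mean follow-up log viremia, the ratio of their SDs, and the baseline SD.

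**1. Reproduce the plan.** With the exact non-central t, the non-centrality is d / (SD × √(2/n)).

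- 1 log, SD 1: 14 per group gives 82.4% power, so 14 is the smallest n above 80%. The stated figure is confirmed.
- 0.7 log, SD 1, 25 per group: 0.7 / √(2/25) = 2.475 on 48 df gives 78.7% power. The difference detectable at 80% is 0.714 log. Both agree with the stated 0.7 after rounding.
- 1 log, SD 1.4, 25 per group: 80.1%.
- 1 log, SD 1, 25 per group: 96.7%.

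**2. Gain from ANCOVA.** Let sb and sf be the baseline and follow-up SDs.

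- Change-score variance: sb² + sf² − 2·r·sb·sf
- ANCOVA residual variance: sf²(1 − r²)
- With sb = sf, the ratio of the second to the first is (1 + r)/2.

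The cost of two covariates is charged as 46 df and a variance inflation of 1 + 2/45 = 1.044 for expected chance imbalance. Infection status is assumed to add nothing beyond baseline viremia. The effective SD is √(ratio × 1.044).

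| Assumed r (equal SDs) | Variance ratio | Effective SD | Power at 0.7 log | Detectable at 80% |
|---|---|---|---|---|
| t-test as planned | 1 | 1.000 | 78.7% | 0.71 |
| 0.3 | 0.65 | 0.824 | 90.6% | 0.59 |
| 0.5 | 0.75 | 0.885 | 86.6% | 0.63 |
| 0.7 | 0.85 | 0.942 | 82.7% | 0.67 |
| covariates explain nothing | 1 | 1.022 | 77.1% | 0.73 |

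The worst case costs 78.7 − 77.1 = 1.6 points. With equal SDs, ANCOVA loses only when r exceeds about 0.91.

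**3. Unequal variances.** Suppose sf = 1.5 × sb (an assumption).

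- r = 0.5: ratio = 2.25 × 0.75 / (1 + 2.25 − 1.5) = 0.964, power 78.4%.
- r = 0.7: ratio = 2.25 × 0.51 / (1 + 2.25 − 2.1) = 0.998, power 77.1%.

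The gain is gone in both. The reason is that the slope r·sf/sb is 0.75 and 1.05, close to the value of one that the change score already imposes.

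**4. Chance imbalance.** The standard error of the baseline difference is sb × √(2/25).

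| Assumed baseline SD | SE of difference | P(difference > 0.3 log) | P(difference > 0.5 log) |
|---|---|---|---|
| 1 | 0.283 | 29% | 8% |
| 1.5 | 0.424 | 48% | 24% |

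Of an imbalance d, the change score passes on (1 − slope) × d. With equal SDs and d = 0.3 log, that is 0.15 log at r = 0.5 and 0.09 log at r = 0.7. These are 21% and 13% of 0.7 log.

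**The case against.** The strongest reply is that nothing here is an error. Randomization makes the unadjusted test valid, the type I error is kept, and the sample size was built for this test and reproduces. The ordinary scatter of baseline imbalance is already in the t-test's standard error. All of this stands.

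The size of the gain also rests on figures that the protocol does not give, and a table with equal variances alone would leave out the case of no gain. That stands too, and step 3 shows that case. Further, the difference used to size the trial is one log. At an SD of one log the t-test already has 96.7% power for it, so adjustment can add at most about 3 points there. The gain matters at 0.7 log, or at one log if the SD is nearer 1.4.

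A reader might infer more than the document supports:

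- **That baseline viremia or prior infection strongly limits the fall.** No assay limit, baseline distribution or correlation is given. Nothing links IgG status to the fall in viremia; the NS1 adjustment concerns a different marker.
- **That ANCOVA can never do worse.** This holds in large samples. Here two covariates that explain nothing cost about 1.6 points.
- **That the whole baseline imbalance reaches the result.** Only (1 − slope) of it does.
- **That adjusting NS1 but not viremia is a contradiction.** The NS1 variable is an absolute level and the viremia variable is referred to baseline, so different models can be defended. The contrast shows only that infection status is available and was thought relevant elsewhere.

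What the objection does not meet is the balance of cost and benefit. The covariates are collected anyway, and the possible loss is small and bounded.

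**Conclusion.** The point holds as one of efficiency and robustness, not of validity. The protocol fixes an unadjusted comparison while holding the baseline data that could sharpen it, and its randomization does not balance the arms on those data.

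With equal variances, power at 0.7 log would rise by about 12, 8 or 4 points at r = 0.3, 0.5 or 0.7. With follow-up SD 1.5 times baseline SD and r of 0.5 or more, there would be no gain or a loss of up to about 1.6 points. The document does not say which case applies, so no single figure for lost power can be claimed. The case for adjusting is an uncertain gain that may be useful, set against a small and bounded cost. It is strengthened by power that is close to 80% at 0.7 log, with no allowance for dropout and no replacement of patients who withdraw.

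**What to change.** Before unblinding, amend the primary outcome paragraph of the protocol, and carry the same wording into the SAP. The primary virological analysis becomes an ANCOVA of mean log reduction over Days 2 to 4 on treatment, baseline log viremia and primary versus secondary infection, with a one-sided 5% test of the treatment term. Keep the two-sample t-test as a supportive analysis. With baseline log viremia in the model, the treatment estimate is the same whether the outcome is the reduction or the follow-up mean (apart from sign), so the stated endpoint need not change.

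The cost is a wording change, two degrees of freedom, and at most about 1.6 points of power if the covariates explain nothing. The sample size, the blood draws and the randomization stay as they are.
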